### Data collection for quantitative surveys

The DSS data collection and recording system will be used. This is a comprehensive system in which all households have been mapped and given a unique number. All members of each household are known. Each village has a trained data collector and every five to six field assistants have a field supervisor and a local community key informant. A team of local enumerators have already mapped the 18 parishes using geographical information systems (GIS), identified and allocated a unique identification number to every household (defined as a group of individuals sharing one kitchen), did a baseline census of demographic and socio-economic indicators, and generated a list of female household members according to predefined written protocols. During the thrice-yearly update rounds questions are asked of all females 12 to 50 years of age, whether they are pregnant and approximate age of the pregnancy estimated. This pregnancy registration is then followed up in the next update round for birth outcome. In addition, community key informants report births to the DSS staff.

Repeated surveys of practices are done twice per year. Each survey takes some three months to complete. Based on pregnancy recording from the DSS round and birth reports by community key informants at the estimated end of the neonatal period, a field worker will visit the woman to interview on practices during pregnancy, delivery and the first month of life. The interview will include details of any preceding pregnancy, home-care practices, exposure to the CHW home visits, and use of health services for neonatal illness. The questionnaires will be written in English and translated into the local language, Lusoga, and the accuracy of the translation will be checked by back translation into English. Medical experts will review the questionnaire for content validity. Interviewers will administer the survey in Lusoga, the local language. The survey will be pilot tested among 20 mothers outside the DSA and the resulting suggestions regarding clarity and cultural appropriateness will be incorporated.

Field editing will be done. After correction, data will be double-entered into a relational database management system.

### Data analysis

The detailed analysis plan for the trial will be finalized during the evaluation preparation phase. For the qualitative study, content analysis will be used for data analysis and emerging themes arranged into categories. NVivo version software (QSR International, Melbourne Australia) will be used for the analysis.

Quantitative analysis of practice variables will use descriptive univariate analysis for all variables separately, then an intention-to-treat approach comparing summary variables in the intervention to control clusters. However, the effects of the health facility strengthening will be assessed in the control clusters using a ‘before-after’ approach. Outcomes will be compared with adjustment for clustering using appropriate Stata commands (svy). For 2×2 cross tabulations containing cells with expected frequencies of fewer than 5, statistical significance will be determined using Fisher’s exact test, the method consists of evaluating the sum of probabilities associated with the observed table and all possible 2×2 tables that have the same row and column totals as the observed data but exhibit more extreme departure from independence; Yates’ corrected chi square will be used for all others when testing for independence in a contingency table. For cross tabulations with greater than 2 rows, statistical significance will be determined using the Pearson chi square test.

Analysis of variance (ANOVA) will be used for statistical comparison of means. Randomized experiments suggest that ANOVA is particularly appropriate for the analysis of data from experiments in which each subject/individual in the experimental unit is randomly assigned to one of two or more different treatment conditions (control and intervention groups). All subjects in a particular group will receive the same treatment, and differences in the effects of the treatments (control and intervention) are expected to produce differences between groups in post-treatment scores on a relevant measure.

In midterm evaluation, in order to see who is and who is not receiving the intervention, we will carry out analyses using important criteria such as: reach/coverage (who is receiving and not receiving the intervention and what are their characteristics) (data to come from the surveys we are planning from ‘exposure to CHW intervention’ variable); and fidelity (the extent to which the intervention is delivered as originally defined.

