**Figure 1 F1:**
[figure not shown]
Map showing the location of Iganga-Mayuge districts and the Demographic Surveillance Area, Uganda.

The Iganga-Mayuge DSS started its operations in 2004 as collaboration between Makerere University and the Karolinska Institutet, Sweden on one hand, and the two host districts on the other, with seed funding from Sida/SAREC. The Demographic Surveillance Area (DSA) has a population of about 67,200 people in 63 villages, 18 parishes and 12,000 households.

Through household visits, field assistants record pregnancies, pregnancy outcomes, deaths and migrations. Since November 2005, village-based demographic scouts notify DSS verbal autopsy interviewers (VAI) of all deaths in the area as they occur on a continuous basis. The VAI visit the bereaved family a month after the event and interview a relative of the deceased who was present at the time of the illness/event and death on verbal and social autopsies (VASA). Three experienced practising doctors independently review the data and assign differential diagnoses on the cause of death according to standard criteria. If there is agreement between at least two of them, the diagnosis is accepted as the definitive cause of death. However, if they do not agree, the three doctors meet to discuss the case and attempt to reach agreement. If this is not possible the cause is coded as undetermined. Besides determination of the most prevalent causes and circumstances of death, we also use the data to profile the burden of different disease, including neonatal conditions. This data from the VASA for maternal and newborn deaths will be analysed as part of the formative research. Results will be used to identify areas in the social processes leading up to death and hence identify modifiable factors in the home or health system on which interventions can be designed.

Iganga Hospital and 13 small health units of which 2 conduct deliveries are located in the DSA. Preliminary findings from the DSA show the following: that 60% of all deaths occur outside a health facility setting; almost all (90%) deaths are due to illnesses as opposed to other causes like injuries and suicide; and the stillbirth rate is about 10/1,000 births, thus indicating under-detection of negative birth outcomes. As it is for most DSS, the first analysis has been a learning experience on the quality of the data, particularly on the reporting of pregnancies, births and newborn deaths.

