### Sample and sample size

To evaluate the effect of the intervention, practice differences and changes will be determined as differences in proportions between intervention and control areas. With 80% power and 95% significance level to detect, for example, an increase in attendance four times at ANC from 40% to 60% assuming a coefficient of variation (k) of 0.25 between clusters (parishes), this will require some 60 interviews per cluster in each intervention arm for each practice survey. Similarly, to detect an increase in skilled attendance at birth from 30% to 50%, again with a k of 0.25, some 25 interviews have to be performed. To detect in increase in postnatal care from 12% to 24%, with a k of 0.25, some 30 mothers have to be interviewed. Note that the study is not powered for mortality evaluation. The number of clusters was fixed *a priori* because those were the available ones, and the sample size estimations mainly focused on the cluster size for each outcome for an 80% power.

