### Overview of the trial design

#### Randomization

The unit of intervention and randomization was the village. The study area has 63 villages. All the 63 villages were eligible for randomization. Given the relatively large number of study units (63), we proposed not to stratify or match. Allocating 31 villages to intervention and 32 to comparison we thus have 31 units of intervention, each with 1 to 3 CHWs depending on the number of households therein (Figure 2). Given that the intervention is primarily through home visits by the CHW, we never anticipated contamination to be a big problem, since that would imply making extra home visits. This, however, would be monitored in the annual coverage surveys proposed. Spillover by word of mouth woman-to-woman or other would be captured as a secular trend in the comparison villages. Statistically, we believe it is advantageous to keep the unit of intervention and randomization the same. We also avoid the complexities of which outcome measure to match/stratify on.

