### Hypothesis testing

The primary analysis for each outcome will be intention-to-treat, which will be defined by a woman’s village of residence. All analyses will account for the cluster-randomized design using random effects logistic regression and will be carried out both with and without adjustment for potential confounders. The estimated effect of the intervention will be presented as a relative risk together with a 95% confidence interval (CI). Logistic regression will be used to explore whether the hypotheses stated below are true or not, and each will be adjusted for intraclass correlation (ICC), coefficient of variation (k), socio-economic status and other potential confounders. The hypotheses are that: the intervention increases

1. % of pregnant women attending ANC at least four times (from 40% to 60%)

2. % of pregnant women who get a skilled attendance at delivery (from 30% to 50%);

3. % of mothers and babies who receive postnatal care (from 12% to 50%).

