### Additional analyses

GIS and socio-economic data are already being collected in the DSS and thus provide a good opportunity to undertake these analyses. In the control area, data analysis will also be done by doing a before-and-after comparison to estimate the effect of only health facility improvement on maternal and neonatal care facilities. Subgroup analyses estimating separate intervention effects for facility- and home-based deliveries.

Analysis will also be done taking account of the quality of the intervention received, as assessed by the process indicators and number of visits received. Because some study participants are highly mobile and some women will move from their place of residence to their parents’ or in-laws’ houses for delivery of the baby, it is envisaged that there may be significant movements across the arms of the trial (that is, some women will move from intervention to control areas and vice versa) during the intervention period. This movement can be tracked using our surveillance system. Thus we will also compare outcomes subdividing women and newborns into the following groups: whether the visits were only pre-delivery or only post-delivery or both, and whether the woman received all five visits, only four, three or two or less visits. However, the main analysis will be based on intention to treat so women who are enrolled in an intervention area, but move to a control area for delivery, will be included in the intervention group.

In addition, analysis will also be done of the mean practice score (a numerical outcome) will be carried out using random effects (multilevel) models that explicitly model the similarity between individuals in the same cluster; (these are not suitable for binary outcomes).

For all statistical determinations, significance levels will be established at 5% level of significance. Coefficient of variation will be reported.

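### The Data analysis section leaves unclustered significance tests (Fisher, Yates/Pearson chi-square, ANOVA) beside the clustered primary model and justifies ANOVA by individual randomisation that did not take place

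*Protocol article*

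**What the plan says.** The Randomization section is clear about the design: "The unit of intervention and randomization was the village", with 31 villages in one arm and 32 in the other.

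The Data analysis section first promises that outcomes will be compared with adjustment for clustering through Stata's svy commands. It then lists tests that have no cluster term. Fisher's exact test determines significance in two-by-two tables with small expected counts. For the other two-by-two tables, Yates' "corrected chi square will be used for all others when testing for independence in a contingency table". Pearson's chi-square covers tables with more than two rows, and ANOVA compares means. The reason given for ANOVA is that "ANOVA is particularly appropriate for the analysis of data from experiments in which each subject/individual in the experimental unit is randomly assigned" to a treatment condition, and the text names the control and intervention groups.

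The Hypothesis testing section sets a different rule: "All analyses will account for the cluster-randomized design using random effects logistic regression". The Additional analyses section gives the mean practice score a multilevel model and adds in brackets that "these are not suitable for binary outcomes".

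**The concern.** Fisher's test, the chi-square tests and one-way ANOVA on individual women treat women from the same village as independent. When whole villages are allocated, the between-village variation belongs in the standard error of the arm difference. Leaving it out makes the p-value too small.

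The rationale for ANOVA describes a trial in which individuals were assigned, which is not this one. Means are also given two methods: ANOVA in Data analysis and a multilevel model in Additional analyses.

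A reader who follows the text literally could produce two p-values for one outcome, one clustered and one not, with nothing in Data analysis to say which governs. The exposure is greatest for the long list of practice outcomes under Primary outcomes and in Table 4, because only three outcomes are tied by name to the clustered model. The results are meant to inform scale-up in Uganda, so false positives among those outcomes matter.

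**Working it through.** **Inputs from the protocol article**
- k = 0.25, from Sample and sample size: "assuming a coefficient of variation (k) of 0.25 between clusters (parishes").
- 60 interviews per cluster for four ANC visits (40% to 60%), 25 for skilled attendance (30% to 50%), 30 for postnatal care (12% to 24%), from the same section.
- "63 villages, 18 parishes and 12,000 households", from Study site.
- 5% significance level, from Additional analyses.

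**Reproducing the plan's own figures.** For c clusters per arm, the usual formula for proportions solves to

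m = [p0(1−p0) + p1(1−p1)] / [(c−1)(p0−p1)²/(1.96+0.84)² − k²(p0²+p1²)].

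With c = 9 (18 parishes halved, which is inferred), two-sided 5% and 80% power, m = 58.0, 23.6 and 28.3, against the stated 60, 25 and 30. So k and the interview numbers are parish figures.

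**Moving to villages (assumptions).** The interviews per village are not stated. Sixty per parish over 18 parishes, spread across 63 villages, gives 60 × 18/63 = 17.1, taken as 17. The same women are assumed to answer for all outcomes in a survey. k = 0.25 is assumed to hold between villages.

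**Formulas.** ICC = k²p/(1−p). Design effect DE = 1 + (m−1) × ICC. True type I error of a nominal 5% unclustered test = 2[1 − Φ(1.96/√DE)].

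| Prevalence p | m | ICC | DE | Type I error |
|---|---|---|---|---|
| 40% | 17 | 0.0417 | 1.67 | 12.9% |
| 30% | 17 | 0.0268 | 1.43 | 10.1% |
| 12% | 17 | 0.0085 | 1.14 | 6.6% |
| 40% | 60 | 0.0417 | 3.46 | 29.2% |

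**Pooling (an assumption; the text does not say that rounds will be pooled).** Two rounds give m = 34. At p = 40%, DE = 1 + 33 × 0.0417 = 2.38 and the error is about 20%, if women in one village are as alike across rounds as within them.

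**Effect of Yates' correction.** The formula ignores it, so the null was simulated with beta-binomial data, 31 against 32 villages, k = 0.25 and 40,000 runs per setting.

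| p | m | Formula | Yates, simulated |
|---|---|---|---|
| 40% | 60 | 29.2% | 28.3% |
| 40% | 20 | 14.3% | 13.2% |
| 40% | 10 | 9.5% | 7.9% |
| 30% | 25 | 12.6% | 11.6% |
| 12% | 30 | 7.9% | 6.9% |
| 12% | 10 | not run | 4.5% |

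A t-test on village proportions gave 4.9% to 5.0% in every setting.

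**The case against.** **A clustered primary test is already named.** This stands. Hypothesis testing defines the primary analysis for each outcome by village of residence and requires the random effects logistic model. A reader might infer that the trial has no valid primary test; the documents do not support that. The defect is conflicting text beside a valid model.

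**Fisher and Yates are never tied explicitly to arm comparisons.** Also correct. Data analysis also plans descriptive work, a before-after comparison in control clusters and tables of who is reached. The link to arms is explicit only for ANOVA. For the table tests it is inferred from their place straight after the sentence on comparing outcomes, and no sentence limits them to other tables.

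**The bracket in Additional analyses need not disown the primary model.** A reader might take it to say that random effects models in general cannot handle binary outcomes, which would contradict Hypothesis testing. But it closes a sentence about models for a numerical score, so it can mean linear multilevel models only, and then it is right. It is ambiguous rather than plainly wrong.

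**The inflation is easily overstated.** The 29% needs 60 women per cluster, a parish figure. At the national birth rate of 47.8 per 1,000 (assumed to apply here), 67,200 people in 63 villages give 67,200 × 0.0478/63 = 51 births per village a year, about 25 per half-year. Sixty per village in one of the twice-yearly surveys is therefore out of reach. A calculation at 50% prevalence would use a target value, not a baseline. For rare outcomes with few interviews there is no inflation (4.5% simulated).

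**A detailed analysis plan is still to come.** That excuses missing detail. It does not correct a wrong design rationale or tests already fixed in print.

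**Conclusion.** The point holds as an internal contradiction with a false design rationale. Data analysis assigns significance to tests that ignore the village and supports ANOVA by individual assignment, against the svy adjustment in the same section, the clustered model in Hypothesis testing and the multilevel model in Additional analyses.

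The primary model is not in doubt. The risk is the alternative p-value, mainly for outcomes beyond the three named hypotheses and for means. For one survey its true error is about 13%, 10% and 7% at the three baseline prevalences of 40%, 30% and 12%, and slightly less with Yates' correction. These figures rest on k = 0.25 carrying over from parishes to villages and on about 17 interviews per village. A smaller k or fewer interviews lowers them, and pooling rounds raises them.

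**What to change.** 1. In Data analysis, delete Fisher's exact test, Yates' and Pearson's chi-square and ANOVA as tests between arms, or limit them expressly to tables that do not compare arms.
2. Delete the argument that ANOVA suits individually assigned subjects.
3. State that every arm comparison takes the village as the cluster: the random effects logistic model already in Hypothesis testing for binary outcomes, the linear mixed model already in Additional analyses for the practice score, and a t-test on village summaries or a permutation test over the village allocation for sparse outcomes.
4. Reword the bracket in Additional analyses to say that linear mixed models are for the numerical score and random effects logistic regression is for binary outcomes.

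The cost is wording only: no new data and no change to design or conduct. Some p-values will be less favourable than those from the unclustered tests.

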### Hypothesis testing

The primary analysis for each outcome will be intention-to-treat, which will be defined by a woman’s village of residence. All analyses will account for the cluster-randomized design using random effects logistic regression and will be carried out both with and without adjustment for potential confounders. The estimated effect of the intervention will be presented as a relative risk together with a 95% confidence interval (CI). Logistic regression will be used to explore whether the hypotheses stated below are true or not, and each will be adjusted for intraclass correlation (ICC), coefficient of variation (k), socio-economic status and other potential confounders. The hypotheses are that: the intervention increases

1. % of pregnant women attending ANC at least four times (from 40% to 60%)

2. % of pregnant women who get a skilled attendance at delivery (from 30% to 50%);

3. % of mothers and babies who receive postnatal care (from 12% to 50%).

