#### Dissemination phase

To inform on the design and scale-up of community-based mother-newborn care in Uganda.

**Hypothesis: H1:** Implementation of an integrated care package of five home visits by a CHW during pregnancy and the neonatal period to deliver one-on-one health messages and promote linkage to the health facility improves the following maternal-newborn care practices by at least 20% in two years amongst the target population in rural Uganda:

• % of pregnant women attending ANC at least four times (from 40% to 60%);

• % of pregnant women who get a skilled attendance at delivery (from 30% to 50%);

• % of mothers who put nothing on the cord (to get baseline figures during formative research);

•% of newborns who are managed in skin-to-skin contact after delivery (to get baseline figures during formative research);

• % of mothers and babies who receive postnatal care (from 12% to 50%).

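### A relative risk is promised from a random effects logistic model, but no step is stated that turns the model's odds ratio into one

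*Protocol article*

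**What the plan says.** Three statements in the protocol article's Hypothesis testing section bear on this.

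- The model: "All analyses will account for the cluster-randomized design using random effects logistic regression", run with and without adjustment for confounders.
- The effect measure: "The estimated effect of the intervention will be presented as a relative risk together with a 95% confidence interval (CI".
- The test of the hypotheses: "Logistic regression will be used to explore whether the hypotheses stated below are true or not, and each will be adjusted for intraclass correlation (ICC". The coefficient of variation k, socio-economic status and other confounders follow in the same list.

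The hypotheses listed there are antenatal care (ANC) at least four times, 40% to 60%; skilled attendance at delivery, 30% to 50%; and postnatal care, 12% to 50%. H1, under Dissemination phase, says the package "improves the following maternal-newborn care practices by at least 20% in two years".

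Elsewhere, Sample and sample size says effects will be determined as differences in proportions between the arms, and it uses 12% to 24% for postnatal care. Data analysis names Stata survey commands, chi-square tests and Fisher's exact test without an effect measure, and says the detailed analysis plan is still to be finalised. Additional analyses applies random effects models to the mean practice score, adds that they are unsuitable for binary outcomes, and says the coefficient of variation will be reported.

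**The concern.** The article fixes both a model and a reporting scale, and the two do not meet without a further step. Exponentiating the treatment coefficient of a random effects logistic model gives an odds ratio comparing women in the same or an equivalent cluster. It is not a ratio of proportions. Several standard methods lead to a risk ratio: averaging predicted risks, a log-link or modified Poisson model, or a ratio of cluster-level risks. None of them is named.

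The step matters because the outcomes are common. Between 12% and 60% an odds ratio does not approximate a relative risk. The trial is meant to inform scale-up, so its readers will take a figure labelled relative risk at face value.

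Two smaller points sit in the same text. The remark under Additional analyses, as worded, rules out the kind of model that Hypothesis testing prescribes for binary outcomes. And the ICC and k are listed beside socio-economic status as things to adjust for, although they describe variation between clusters and are not covariates.

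**Working it through.** The article gives no odds ratio or relative risk to reproduce. Its own figures on this point are the pairs of proportions.

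**Inputs.** Three pairs (p0, p1) from Hypothesis testing: 0.40 and 0.60, 0.30 and 0.50, 0.12 and 0.50. A fourth, 0.12 and 0.24, from Sample and sample size, which also gives k = 0.25.

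**Step 1: odds against risk.** RR = p1/p0. OR = [p1/(1 − p1)] / [p0/(1 − p0)]. Hence OR/RR = (1 − p0)/(1 − p1).

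- 40% to 60%: RR = 0.60/0.40 = 1.50. OR = 1.5/0.6667 = 2.25. OR/RR = 0.60/0.40 = 1.50.
- 30% to 50%: RR = 0.50/0.30 = 1.67. OR = 1/0.4286 = 2.33. OR/RR = 0.70/0.50 = 1.40.
- 12% to 50%: RR = 0.50/0.12 = 4.17. OR = 1/0.1364 = 7.33. OR/RR = 0.88/0.50 = 1.76.
- 12% to 24%: RR = 0.24/0.12 = 2.00. OR = 0.3158/0.1364 = 2.32. OR/RR = 0.88/0.76 = 1.16.

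**Step 2: the part due to conditioning on the cluster.** Take logit(risk) = a + b·arm + u, with u normal, mean 0 and SD s. Choose a and s so that the control-arm mean risk is p0 and the between-cluster SD of risk is 0.25·p0. Choose b so that the intervention-arm mean risk is p1. The cluster-specific odds ratio is exp(b). The integrals were evaluated by Gauss-Hermite quadrature.

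| Effect | s | Marginal OR | Cluster-specific OR | Cluster-specific / marginal | Cluster-specific / RR |
|---|---|---|---|---|---|
| 40% to 60% | 0.434 | 2.25 | 2.33 | 1.037 | 1.56 |
| 30% to 50% | 0.365 | 2.33 | 2.40 | 1.026 | 1.44 |
| 12% to 50% | 0.283 | 7.33 | 7.56 | 1.031 | 1.81 |
| 12% to 24% | 0.283 | 2.32 | 2.34 | 1.010 | 1.17 |

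Conditioning on the cluster adds about 3% to 4% at the hypothesised effects and 1% at 12% to 24%. The rest of the gap is odds against risk.

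**Step 3: what a reader would see.** For four ANC visits, an odds ratio of 2.25 read as a relative risk suggests a 125% increase, where 40% to 60% is a 50% increase.

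**Step 4: the scale of the hypothesis.** 60 − 40 = 20 and 50 − 30 = 20, so the 20% in H1 is in percentage points. A 20% relative rise from 40% would reach only 48%. The quantity that answers H1 directly is a risk difference, which Hypothesis testing does not name.

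**The case against.** The other side has a good deal on its side.

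- A reader might infer that the named model cannot produce a relative risk, so that the promised estimate does not exist. The documents do not support that: averaging predicted risks from a logistic model gives one. What is missing is the link, and a journal article that leaves its detailed analysis plan for later may omit such detail. This limits the point but does not remove it, because the article itself fixes both the model and the scale, and a plan that follows the text literally inherits the gap.
- A reader might also infer that an inflated effect will be published. Nothing says so. The article never mentions an odds ratio, and the overstatement arises only if one is labelled or read as a relative risk. The null hypothesis of no effect is the same on either scale.
- The cluster-specific nature of the odds ratio is a minor part of the gap, as Step 2 shows. That the random effect is at village level is inferred from the unit of randomisation; Hypothesis testing does not give the level.
- The absolute scale is not absent, since the sample size section speaks of differences in proportions. Making the risk difference the primary measure would be a preference, not a correction.
- The remark about binary outcomes may have been meant for linear models of a numerical score. That is a fair charitable reading, but the words do not say it.
- Adjusting for the ICC and k most likely means allowing for clustering. That is plausible, and the point is one of wording.

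**Conclusion.** The point holds as a mismatch in the article's own text: a logistic model with cluster effects, a relative risk as the reported effect, nothing to join them, and a remark elsewhere that as worded disallows the model. If the odds ratio is taken for the relative risk, the ratio is overstated about 1.4 to 1.8 times at the hypothesised effects and about 1.2 times at 12% to 24%.

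The size rests on two assumptions: that the observed proportions are near the planned ones, and, for the small clustering part only, that k = 0.25 applies at the level of the random effect. The article states that k for parishes, whereas villages were randomised. A larger village-level k would raise the clustering part; the odds-against-risk part does not depend on it.

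The conclusion concerns what is estimated and how it is labelled. It does not touch the design, the data collection or the validity of testing for no effect.

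**What to change.** In Hypothesis testing:

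1. State that the relative risk is a marginal risk ratio between arms, and name one method. One option is to standardise the logistic model's predicted risks over the study population, averaging over the random effect rather than setting it to zero, with a village-level bootstrap or delta-method interval. The other is a modified Poisson or log-link GEE clustered on village. Use the same method for the unadjusted and adjusted estimates.
2. Report the risk difference in percentage points beside it, in line with the sample size section and the targets in H1.
3. State that the random effect or clustering is at village level.
4. Delete the ICC and k from the adjustment list and report both as estimates. Reporting of k is already promised.

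In Additional analyses, reword or remove the remark on binary outcomes so that it no longer conflicts with the primary model.

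If an odds ratio is to be reported as well, label it as such. The cost is a few lines of text and standard code, with no new data, and it should be settled before outcome data are analysed.
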